**Figure 2 figure2:**
[figure not shown]
Flowchart describing how individual participants will progress through the phases of the research.

### Data Management

#### Data Management and Monitoring

All study data will be collected and recorded electronically through the Black Dog Institute Research Engine. The servers are hosted in a secure environment (Amazon Web Services) managed by the University of NSW Sydney.

The raw data contain identifiable information (ie, first name, private email address, and mobile phone number) from the registration section at baseline as well as an individual identifier code, which is automatically generated by the system for each participant. Direct individual identifiers will be removed during the transcription process before data preparation and analysis.

Every week, the research team will manually back up all data during the data collection phase; the team will also check that the data are properly archived during every quarter. The backups will be stored in a secure and password-protected University of NSW OneDrive (Microsoft Corporation) folder.

Only the research team approved by our ethics boards (University of NSW Human Research Ethics Committee and Sydney Local Health District Ethics Review Committee) and the designated Black Dog Institute technical staff can access the data. The data will be retained for a minimum of 15 years after the publication of the research findings.

#### Trial Harms and Risk Management

Because the study addresses common mental health concerns and challenges associated with being a junior physician, there is a possibility that a few participants may find it distressing to engage with this content. We do not, however, expect the app itself to result in more serious harm, and there were no adverse or serious adverse events registered in the preceding app trials [14]. We define adverse events as any event in which a participant contacts the Shift research team with the indication that the app has had a harmful effect on their health, including any level of psychological distress. The principal investigator will keep a record of all adverse events and inform both the approving ethics committees (the University of NSW Human Research Ethics Committee and the Sydney Local Health District Ethics Review Committee) within 24 business hours following an adverse event. A data safety monitoring board will review the safety protocol and risk management plan. If any risks or adverse events emerge during the trial, the board will meet to review the continuing safety of the study. The board will consist of 3 reviewers who are not associated with the RCT and have a clinical background. If a serious adverse event or reaction is reported, or several adverse events or reactions, the study’s data safety monitoring board will review the impact of the study on the participants, and the study may be terminated if the board determines the study is harmful to participants.

When participants initially access the study website, they are presented with the participant information statement and consent form in which the study risks are outlined and emergency helpline contact details are provided. In this form, participants are also provided with the contact details of the research team. If participants contact the research team expressing any level of psychological distress or requesting further support, the team will arrange a callback from the Black Dog Institute’s Clinical Services to ensure that appropriate care is being offered to the participant.

On every page of the study website, including the web-based questionnaires, a banner with emergency-contact details is presented at the bottom of the page. These details can be used by the participants if they are experiencing psychological distress. Furthermore, the participants who have medium or high scores (suggesting medium or severe ranges for depression and anxiety) or indicate having suicidal thoughts while responding to the depression measure will see a pop-up window that informs them of their scoring result along with suggestions on how to seek help through a designated helpline. They are also advised to consider making an appointment with their general practitioner or a mental health professional if their symptoms increase or persist.

The app features an in-built “reach out” button at the top right-hand corner of the home screen to support participants who may become distressed while using the app. This button takes users directly to contact details for mental health services and 24×7 telephone helpline numbers. Furthermore, the participants who score poorly on the daily mood checkups (those who select the response options “worse than usual” or “slightly worse than usual”) are provided with suggestions to access mental health support options.

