## Methods

### Study Design

The study is a 2-arm parallel RCT. Randomization is not stratified and will automatically occur when a participant completes the baseline questionnaire. The study will be carried out entirely on the internet and will not be blinded due to the nature of the intervention.

Junior physicians will be randomly allocated to one of two groups, namely, (1) the intervention group or (2) the control group. The intervention group will be provided with a link to download the Shift mHealth app; the participants in this group will be asked to use the app for a period of 30 days. The control group will be placed on a waitlist and will be asked to use the app after 3 months. Participants allocated to the control group are provided with a factsheet that lists several mental health support services, which they are encouraged to contact for further support. These participants will gain access to Shift after 3 months and will be asked to use the app for 30 days.

Primary and secondary outcomes will be measured through self-assessment using questionnaires at 3 time points: the first distributed as part of the baseline assessment, the second distributed 30 days after the baseline assessment, and the third distributed 3 months after the baseline assessment. Waitlist control participants will be further asked to respond to a questionnaire measuring primary and secondary outcomes after 4 months following the baseline assessment or 1 month after they gain access to the app. This will enable us to compare the 30-day app use patterns of the control group with those of the intervention group who used the app in the first month of the trial.

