### Study Setting and Recruitment

Data collection will occur between January and August 2024; recruitment will occur using 3 strategies. Firstly, participants will be recruited through the Black Dog Institute’s web-based and social media channels including webpages on the Black Dog Institute website and targeted social media advertisements on Facebook (Meta Platforms, Inc) and Instagram (Meta Platforms, Inc). Secondly, the NSW Ministry of Health will disseminate study information through NSW Health public health systems. NSW is the state in which the greatest proportion of junior physicians in Australia are employed, primarily through public hospitals. Thirdly, the research team will partner with private medical colleges and other medical specialist organizations based in Australia to disseminate study information on medical platforms. Promotional materials may include the logos of the Black Dog Institute, the University of NSW Sydney, and NSW Health.

The inclusion criteria for participants taking part in this study include the following: (1) The participant must be currently working as a junior physician (ie, intern, hospital medical officer, resident medical officer, nonaccredited trainee, postgraduate trainee, principal house officer, registrar, or specialist trainee) in Australia. (2) The participant must own an internet-enabled smartphone that has an iOS (Apple) or Android (Google) operating system. (3) The participant must provide consent to participate.

Candidates who do not meet all the 3 eligibility criteria will be excluded from participation. Instead, they will be provided with mental health support options and information on other current research projects run by the Black Dog Institute.

The study is conducted remotely and occurs entirely on the web for all participants. This means that there is no direct contact with the research team unless a participant voluntarily contacts the team using contact details in the participant information statement and consent form.

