### Procedure

The procedure for the Shift RCT is depicted in Figure 2. At the study sign-up, candidates will be invited to visit a study-specific website [24]. Through the website, they will be presented a brief overview of the study purpose and the full participant information statement and consent form. The candidates who are willing to participate will be able to self-screen for eligibility. All the eligible participants will then be presented with a registration page in which they will be asked to input their first name, email address, mobile number, and password.

Following registration, the participants will be asked to complete a survey assessing the primary outcome (depression) and secondary outcomes (anxiety, work and social functioning, quality of life, burnout, and help-seeking intentions and behaviors). After completing the baseline survey, the participants will be randomly assigned to (1) the intervention group (in which a link will be provided through which they can download and use the app, immediately after registration) or (2) the waitlist control group (the members of will be added to a waitlist to use the app). The participants in the waitlist control group are provided with a factsheet listing contact details for several mental health support services and are encouraged to reach out if they would like further support. After the 3-month study period, the participants in the control group will also gain access to the app and will be asked to use it for 30 days. After the participants are provided with a link to download the Shift app on their smartphone, they will be able to use the app free-of-cost.

The primary and secondary outcomes will be measured in both the control group and the intervention group at a number of time points: at baseline and registration (time point 1), 30 days after registration (time point 2), and 3 months after registration (time point 3). These outcomes will also be measured among participants in the control group after 4 months following registration (time point 4), that is, once the participant has had access to the app for 30 days. At each follow-up measurement time point, the participants will receive an initial email reminder to complete the study. This will be followed by an email, a text reminder after 2 days and a text reminder after 9 days.

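### During the 3-month randomised comparison, waiting controls cannot meet the adverse event definition, and individual PHQ-9 worsening in either arm is not described as a harm outcome

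*Protocol article*

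**What the plan says.** The definition is in Trial Harms and Risk Management. An adverse event is one in which a "participant contacts the Shift research team with the indication that the app has had a harmful effect on their health", and distress of any degree is included. The threshold of severity is low, but the participant has to start the contact and link the harm to the app.

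Study Setting and Recruitment describes a fully remote trial in which "there is no direct contact with the research team unless a participant voluntarily contacts the team". Study Design gives the waitlist condition: "The control group will be placed on a waitlist and will be asked to use the app after 3 months". Procedure adds a later assessment of this arm only: "These outcomes will also be measured among participants in the control group after 4 months following registration (time point 4").

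PHQ-9 is collected in both arms at baseline, 30 days and 3 months (Procedure; Table 1). On the same questionnaire, participants with medium or high scores and those who "indicate having suicidal thoughts while responding to the depression measure will see a pop-up window" with their result and help-seeking advice. A participant who contacts the team in distress is offered a clinical callback. The article does not say that the score, the suicidal-thought response or the callback is recorded as an adverse event or tabulated by arm.

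A data safety monitoring board meets if risks or adverse events emerge, and "the study may be terminated if the board determines the study is harmful to participants".

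Under Primary Outcome, PHQ-9 is compared between arms as mean change and as caseness (10 or more). One stated aim is to see whether well participants stay well.

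**The concern.** A harm measure for a randomised trial should be capable of being met in both arms, so that the control arm supplies the background rate. Here attribution to the app is part of the definition, and one arm has no app during the comparison. Whatever number the intervention arm produces, it has no concurrent control rate beside it.

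The definition is also passive. Someone who gets worse, does not blame the app or does not write in, and simply stops responding is not an event. The article expects substantial attrition, so this is a realistic course.

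What is at stake is how the safety result can be read. A report of few or no adverse events would say little about whether the app arm deteriorated more often than the waitlist arm. A mean benefit on PHQ-9 would not settle it either, because a mean can improve while a minority worsens.

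**Working it through.** **1. Who can meet the definition, and when**

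| Period | Intervention arm | Waitlist arm |
|---|---|---|
| Months 0-3 (randomised comparison) | Has the app; event possible | Not given the app; event not possible if waiting as allocated |
| Months 3-4 | Past the 3-month survey, the arm's last | Has the app; event possible |

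The control count for months 0-3 is therefore zero by rule. Events that controls report in months 3-4 fall outside the randomised comparison and do not supply the missing rate.

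**2. What the planned PHQ-9 analyses show about worsening**

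- *Mean change by arm* averages improvement and worsening together.
- *Caseness* is modelled with arm, occasion, their interaction and a random participant intercept. These contrasts describe how many are cases in each arm at each occasion. Illustration with invented counts: if 20 of 202 participants in one arm cross from below 10 to 10 or more and another 20 cross the other way, the net change is 20 - 20 = 0, although about 10% (20/202) became new cases.
- A participant who starts at 10 or more and worsens stays a case, so caseness does not register the change.
- No separate analysis of the suicidal-thought item is described.

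**3. What a randomised harm table could resolve**

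Inputs from Sample Size: 404 participants without dropout, so 404/2 = 202 per arm; 48% dropout; 778 randomised, so 778/2 = 389 per arm.

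The plan's own figures reproduce. With change-score variance 2(1 - 0.6) = 0.8, d = 0.25, two-sided α of .05 (sidedness assumed) and 80% power, n per arm = 2 × (1.960 + 0.842)² × 0.8 / 0.25² ≈ 201, or 402 in total against the stated 404. Inflation gives 404/(1 - 0.48) = 776.9, so 777, rounded to 778.

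The deterioration rate p is not in the document. I assume 5% to 20%, equal in both arms. The 95% half-width of the risk difference is 1.96 × √(2p(1 - p)/n). With n = 202:

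- p = 5%: 1.96 × √(2 × 0.05 × 0.95/202) = 0.043
- p = 10%: 1.96 × √(2 × 0.10 × 0.90/202) = 0.059
- p = 20%: 1.96 × √(2 × 0.20 × 0.80/202) = 0.078

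The excess detectable with 80% power at 202 per arm is 5% vs 12.9%, 10% vs 19.9% or 20% vs 32.2%, so about 8 to 12 points. If all 389 per arm were observed it would be about 5 to 9 points.

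**The case against.** Several stronger readings are tempting, and the document does not support them.

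- *Controls can never have an adverse event.* Too strong. They receive the app after month 3 and can then meet the definition. Textbox 1 (phase 6) also says the app had earlier been made publicly available, so use outside the trial is not excluded. The point holds for controls waiting as allocated in months 0-3.
- *PHQ-9 worsening is ignored.* It is not. Mean change and caseness are compared by arm, and Secondary Outcomes extends this to 3 months. The aim of seeing whether well participants stay well comes close to an analysis of new caseness. What is not described is individual worsening, newly endorsed suicidal thoughts, or any of these as harm.
- *Following the plan would yield no adverse events even if the app arm did worse.* This does not follow. Any participant who contacts the team and blames the app counts, at any level of distress, and excess caseness could still show in the effectiveness model.
- *The board's judgement rests only on spontaneous contacts.* This cannot be concluded. The board also meets for emerging risks, and the safety protocol and risk management plan that it reviews are not shown. They may provide for more.

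It is also fair to say that the article plans no between-arm comparison of adverse event counts and does not claim that they are comparable. Data collection ended in August 2024, so nothing added now can guide monitoring. A table based on completers could itself miss harm if those who worsened dropped out.

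These points narrow the concern to reporting. They do not change the definition, which is one-sided by a stated rule and not through detail left to another document.

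**Conclusion.** The concern holds in limited form. For months 0-3 the adverse event count has no control counterpart, so it cannot support a between-arm statement about safety, and a low count is not reassurance. The planned effectiveness analyses would pick up a net shift in PHQ-9, but not a worsened minority offset by improvers, worsening among those already at 10 or more, or new suicidal thoughts.

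The primary test is unaffected. A direct comparison would be only moderately precise, about ±4 to ±8 percentage points. That range rests on 202 completers per arm and on an assumed deterioration rate of 5% to 20%. The stated definition gives no comparison at all for this period.

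**What to change.** From data already collected, add one table by randomised arm at time points 2 and 3 with:

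1. the proportion whose PHQ-9 total has worsened from baseline by more than a pre-stated amount;
2. new caseness (10 or more) among those below 10 at baseline;
3. a newly endorsed suicidal-thought item.

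Give each a risk difference and 95% CI. Handle missing data as for the primary outcome, or show the number missing by arm beside each proportion. Fix the worsening amount before tabulating by arm. Analysis was already underway in September 2024, so if arm-level results have been seen, label the table as added afterwards.

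Report the spontaneous adverse events alongside, with a sentence saying that this count is not comparable between arms for months 0-3, and list separately any events that controls report after gaining access.

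The cost is one table and one sentence, with no new data. The downside is modest precision, exposure to attrition, and the possibility that the table shows deterioration that then has to be discussed.

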### Data Analysis

#### Estimands and Statistical Analysis

##### Estimands

The primary estimand [25] will reflect intention-to-treat principles and will be based on all participants in the group to which they were randomized regardless of actual receipt, uptake of the intervention, alternative support or interventions received, and withdrawal from the study. A mixed-model, repeated measures analysis will be used for the primary outcome and continuously scaled secondary outcome variables to estimate and compare the change in mean PHQ-9 score in each intervention arm from time point 1 to time points 2, 3, and 4 (if applicable). This form of analysis assumes that unobserved outcome data are missing at random.

As substantial attrition is expected given the distal, universal nature of the intervention, a sensitivity analysis of the primary outcome will be undertaken if the outcome of the intention-to-treat is statistically significant. The “jump-to-reference” approach will be used [26]. This approach assumes that the participants who withdraw or have no postbaseline data have the same trajectories as participants in the control condition. This will yield a robust, conservative lower bound estimate of the intention-to-treat effect in the presence of missing outcome data.

Secondary estimands will estimate the treatment effect in participants who have engaged with the Shift app to various extents. Given that app users are free to choose the modules they use and to access them as often as desired, the concept of full compliance is not applicable. One estimate will involve participants who complete the recommended 8 or more modules during the intervention. The second estimate will broaden engagement to participants who have completed at least 4 modules. This reflects the levels of engagement more commonly observed in the previous version of the app [14]. The complier average causal effect comparing *compliers* in the intervention group to *would-be compliers* in the control group will be estimated using latent variable methods [27]. A conventional per-protocol analysis, including only participants allocated to the intervention group who have downloaded the app, will also be conducted.

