##### Sample Size

We determined a total sample size of 778 research participants. Power calculations were based on a recent systematic review and meta-analysis quantifying the efficacy of digital prevention interventions for depression [29]. Hence, an estimated Cohen *d* effect size of 0.25, an α value of .05, a power of 0.8, and a correlation coefficient of 0.6 yielded the required sample size of 404, without any participant dropouts.

A systematic review and meta-analysis examining dropout rates during clinical trials of smartphone apps for depressive symptoms found a pooled dropout rate of 48% [30]. Therefore, we expect to randomize a total of 777 participants (N=404+373) to the 2 trial conditions to conduct a sufficiently powered analysis. To allow for evenly sized groups, this number was rounded off to 778 participants.

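### Jump-to-reference is called a lower bound of the intention-to-treat effect, but it is one only if app-arm dropouts fare no worse than control-arm dropouts

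*Protocol article*

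**What the plan says.** The Estimands section of the protocol article fits a mixed model to everyone as randomized and states its missing-data assumption: "This form of analysis assumes that unobserved outcome data are missing at random". Because heavy attrition is expected, it adds that "a sensitivity analysis of the primary outcome will be undertaken if the outcome of the intention-to-treat is statistically significant". The method is jump-to-reference, explained as follows: "This approach assumes that the participants who withdraw or have no postbaseline data have the same trajectories as participants in the control condition". The next sentence draws the conclusion at issue: "This will yield a robust, conservative lower bound estimate of the intention-to-treat effect in the presence of missing outcome data".

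The Sample Size section shows how much rests on this. It relies on a meta-analysis of smartphone-app trials that "found a pooled dropout rate of 48" percent, and it inflates the sample for that loss. The article states no other departure from missing at random.

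**The concern.** Jump-to-reference fills in unseen outcomes under one assumption that the data cannot test. An assumed value is not a bound on what it replaces. If app-arm non-responders did worse than the control trajectory, or control non-responders did better than their arm's completers predict, the true effect lies below the reported figure.

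With about half the outcomes expected to be missing, the sentence would be the trial's main robustness statement. Carried into the results paper, it would tell readers that the effect cannot be smaller than the jump-to-reference estimate. The analysis cannot support that.

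A second, smaller matter is the trigger. Attrition also threatens a non-significant result under missing at random, and as written such a result receives no stated missing-data check.

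**Working it through.** **Inputs.** From Sample Size: "an estimated Cohen *d* effect size of 0.25, an α value of .05, a power of 0.8, and a correlation coefficient of 0.6", and dropout of 48%. From Estimands: dropouts are assigned the control trajectory. The document says nothing about dropouts' real outcomes, so those values below are assumptions, shown as a range.

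**The plan's own figures.** For a two-sided comparison of change scores, the SD is √(2(1 − 0.6)) = 0.894. With d = 0.25, the normal approximation gives 201 per arm (402). The t-based version gives 201.9, so 202 per arm (404), which matches "yielded the required sample size of 404, without any participant dropouts". Then 404 / 0.52 = 776.9, so 777. The sample size reproduces.

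**Algebra.** Effects are in SD units, and positive means benefit. Let p be the dropout share, taken as equal in both arms, and d the benefit among app-arm completers. Let g_a and g_c be the mean benefit of app-arm and control-arm dropouts relative to the outcome predicted from control completers.

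- Jump-to-reference sets g_a = g_c = 0 and returns (1 − p)d.
- True intention-to-treat effect = (1 − p)d + p(g_a − g_c).
- Jump-to-reference is therefore a lower bound only if g_a ≥ g_c. This condition does not depend on p.

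**Numbers.** With p = 0.48 and d = 0.25, jump-to-reference = 0.52 × 0.25 = 0.13, and the true effect = 0.13 + 0.48(g_a − g_c).

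| g_a | g_c | True effect | Against 0.13 |
|---|---|---|---|
| 0 | 0 | 0.130 | equal |
| -0.1 | 0 | 0.13 − 0.048 = 0.082 | below: bound fails |
| -0.2 | 0 | 0.13 − 0.096 = 0.034 | below: bound fails |
| -0.3 | 0 | 0.13 − 0.144 = -0.014 | below: bound fails |
| 0 | +0.2 | 0.13 − 0.096 = 0.034 | below: bound fails |
| 0 | -0.2 | 0.13 + 0.096 = 0.226 | above: bound holds |
| -0.2 | -0.2 | 0.130 | equal: shifts cancel |

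With g_c = 0 the true effect reaches zero at g_a = −0.13 / 0.48 = −0.27 SD. The document gives no PHQ-9 SD. If it is 4 to 6 points (assumption), 0.27 SD is about 1.1 to 1.6 points.

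**Simulation check** (400,000 participants, 48% dropout, correlation 0.6). For g_a = -0.2, g_c = 0, the true effect is 0.039 and jump-to-reference 0.134. For g_a = 0, g_c = +0.2, they are 0.033 and 0.126. For g_a = 0, g_c = -0.2, they are 0.229 and 0.130. Jump-to-reference stays near 0.13 while the truth moves to either side of it.

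**Sensitivity to the dropout share.** At p = 0.30 jump-to-reference is 0.175, and with g_a = -0.1, g_c = 0 the truth is 0.145. At p = 0.60 they are 0.10 and 0.04. The bound fails in the same direction at each share.

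**The case against.** Several points on the other side have force.

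- **The assumption is disclosed.** The sentence before the claim says what jump-to-reference assumes, so a careful reader can see that the result is conditional. That is true, but the conclusion is still worded as a guarantee.
- **The failing case needs a difference between arms.** The Limitations section attributes attrition to lack of time, which applies to both arms, and equal shifts cancel. Trial Harms and Risk Management allows that the content may distress a few participants, but it also reports no adverse events in the preceding app trials. So failure is possible, and the document gives no reason to expect a deficit as large as 0.27 SD. This stands as a limit on likely size. It does not restore the bound.
- **Not all 48% need be set to reference.** Estimands speaks of participants who withdraw or have no postbaseline data. Someone who misses time point 2 but answers time point 3 is not plainly covered, so the shrinkage could be milder than 0.52. This stands.
- **The trigger is coherent for its narrow purpose.** A method that pulls a positive estimate toward the null is naturally used to challenge a significant benefit. This stands for jump-to-reference itself.
- **Further analyses may be in a statistical analysis plan that is not shown.** Their absence from the article is not the fault. The fault is a property that the article claims and the method lacks.

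A reader might go further than the documents allow in two ways. One is to infer that jump-to-reference bounds nothing once control missingness is not at random. The table refutes that: if control dropouts do worse than predicted, the bound holds.

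The other is to infer that jump-to-reference is too weak to confirm a real effect, which would then be dismissed. The article attaches no significance threshold or decision rule to it and names no variance method. With 389 randomized and about 202 observed per arm, an information-anchored standard error of √(2[0.64/202 + 0.16/389]) = 0.085 gives power of about 34%. A repeated-sampling standard error of √(0.52² × 2 × 0.64/202 + 2 × 0.16/389) = 0.050 gives about 74%. The documents do not choose between them.

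**Conclusion.** The concern holds in a limited form. Jump-to-reference is a reasonable conservative scenario, but it is a lower bound only if app-arm dropouts fare no worse than control-arm dropouts relative to the control-based prediction. The article states the bound without that condition.

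On its own figures the analysis returns about 0.13 SD. Under an assumed app-arm deficit of 0.1 to 0.3 SD, the true effect runs from 0.082 down to -0.014 SD. These values rest on equal dropout in both arms, all 48% set to reference, a completers' effect of 0.25 and control dropouts missing at random. The direction of any real departure is unknown, so the guarantee is lost, though the bound may happen to hold.

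Severity is moderate. What is wrong is the interpretation of the only stated departure from missing at random. The primary test, alpha and sample size are untouched.

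**What to change.** 1. In Estimands, delete the lower-bound claim and describe jump-to-reference as one conservative reference-based scenario. It may stay conditional on a significant primary result.
2. Add a delta-adjusted tipping-point analysis of the primary PHQ-9 contrast at time point 2. Vary the shifts separately in each arm over a stated range of PHQ-9 points that includes app-arm dropouts worse than control. Report the combinations at which the conclusion changes.
3. Report that analysis whatever the primary p-value, because a null result with about half the data missing is exposed too. If the statistical analysis plan already contains such an analysis, refer to it and align the wording.

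The cost is a few more multiple-imputation runs, a wording change and a less favourable robustness statement. No further participants or data are needed.
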